|                                                         |                                                                                                                                                                                                                                                                                                                                                                                                                                                                                                                                                                                                                                                                                                                                                                                                                                                                                                                                                                                                                                                                                                                                                                                                                                                                                                                                                                                                                                                                                                                                                                                                                                                                                                                                                                                                                                                                                                                                                                                                                                                                                                                                                                                                                                                          |
|---------------------------------------------------------|----------------------------------------------------------------------------------------------------------------------------------------------------------------------------------------------------------------------------------------------------------------------------------------------------------------------------------------------------------------------------------------------------------------------------------------------------------------------------------------------------------------------------------------------------------------------------------------------------------------------------------------------------------------------------------------------------------------------------------------------------------------------------------------------------------------------------------------------------------------------------------------------------------------------------------------------------------------------------------------------------------------------------------------------------------------------------------------------------------------------------------------------------------------------------------------------------------------------------------------------------------------------------------------------------------------------------------------------------------------------------------------------------------------------------------------------------------------------------------------------------------------------------------------------------------------------------------------------------------------------------------------------------------------------------------------------------------------------------------------------------------------------------------------------------------------------------------------------------------------------------------------------------------------------------------------------------------------------------------------------------------------------------------------------------------------------------------------------------------------------------------------------------------------------------------------------------------------------------------------------------------|
| Sample Size
Determination
and Adjustment | 
The cumulative incidence of the primary endpoint of gastric or small intestinal mucosal lesions within 12 months is estimated to be 47% in patients who received 12 months of DAPT and 30% in those treated with either aspirin or clopidogrel monotherapy beginning at 6 months after enrollment. With a 2:1 ratio in patients treated with either aspirin or clopidogrel monotherapy (the sum of aspirin monotherapy group and clopidogrel monotherapy group) after 6-month DAPT versus DAPT for 12 months, 384 evaluable patients (256 and 128 respectively) provide 90% power to detect a 17% absolute risk reduction (36% relative risk reduction) with a 2-sided type I error of 0.05. Assuming 20% loss of evaluable primary endpoint outcome assessments due to patient withdrawal, loss to follow-up between 6 and 12 months or suboptimal AMCE visualization of the GI tract at 12months, 480 patients are planned to be randomized. Assuming that an additional 10% of enrolled patients will not be randomized at 6 months because of adverse clinical events, non-compliance with antiplatelet therapy, lost to follow-up or withdrawal, 534 patients is required to be initially planned to be enrolled after baseline screening. Finally, assuming that 10% of patients who undergo a screening AMCE examination will be excluded due to unavailable valid image (or definite ulceration and active bleeding), therefore a total of 593 patients is initially planned to be consented and undergo the screening AMCE examination.
 
Among the first 200 patients enrolled, ~25% had gastrointestinal injury at baseline by screening AMCE (despite clinically absent bleeding or gastrointestinal complaints). Of those who passed the initial exam, only ~65% were eligible for randomization; 17% of patients were noncompliant with the 6-month repeat AMCE exam, and new gastrointestinal ulceration or bleeding was found on the 6-month AMCE examination in 18% of patients. The study sample size was adjusted accordingly so 1000 patients will be screened by AMCE at baseline, with 750 patients enrolled and followed to the 6-month randomization eligibility period to achieve the 480 patients randomized goal.
 |

## 1. INTRODUCTION

Antiplatelet therapy (APT) including aspirin and P2Y12 inhibitors has been the cornerstone for prevention of coronary heart disease (CAD), and current guidelines recommend long-term dual antiplatelet therapy (DAPT) with aspirin in combination with one kind of P2Y12 inhibitor after percutaneous coronary intervention (PCI). However, APT may have serious adverse consequences, the most common of which is gastrointestinal mucosal injury with ulceration and bleeding. The frequency of gastrointestinal complications increases with increasing duration of DAPT. Trials in patients treated with contemporary drug-eluting stents (DES) have demonstrated that shortened DAPT regimens reduce the risk of major bleeding with similar ischemic risk. However, whether there is no definite evidence by current studies exploring the difference of gastrointestinal mucosal injuries among different antiplatelet strategies, mainly due to the absence of sensitive, noninvasive and acceptant methods of detecting gastrointestinal injury.

Nowadays, gastroscopy is the most common detection method for gastrointestinal mucosal injury. Although with a good diagnostic accuracy, gastroscopy is an invasive inspection, and have several limitations below in aspect of screening gastrointestinal bleeding: 1) gastroscopy is invasive and is intolerable for patients, therefore only be used to identify the position and reason of bleeding in patients who have experienced major gastrointestinal bleeding, and is lack of early prediction and early warning effect on gastrointestinal injury and bleeding; 2) Because of the fear of major bleeding caused by the mechanical injury of conducting gastroscopy, a large proportion of gastroenterologists usually asked patients to stop antiplatelet therapy for several days before gastroscopy; 3) upper endoscopy can only detect lesions in the stomach and duodenum, as it does not visualize the remainder of the small intestine.

ANKON® magnetically controlled capsule endoscopy (AMCE) is a novel, noninvasive, actively and precisely controlled system which could visualize gastrointestinal injuries in the gamut of esophagus, stomach and small intestine (except colon). The advantages of AMCE includes: 1) Patient acceptance of AMCE is higher than standard endoscopy as the procedure involves only swallowing a small capsule endoscope with non-invasive, painless, convenient and repeatable image observation; 2) Discontinuation of antiplatelet drugs during AMCE is not necessary, as a result of avoiding the risk of stent thrombosis induced by antiplatelet discontinuation; 3) Not only the stomach and duodenum, but the whole small intestine digestive tract can be detected.

Because of the above advantages, this method can be used for the early evaluation of gastrointestinal mucosal lesions associated with bleeding, and can help detect early focal and concealed bleeding, thus playing as an early warning role a guidance for clinical practice. Previous studies have confirmed that the sensitivity and specificity of AMCE for the detection of focal lesions of the gastrointestinal tract are similar compared with standard endoscopy. In this study, we plan to use AMCE as the

evaluation method for gastrointestinal mucosal injury and bleeding, and establish a scoring system for gastrointestinal mucosal injury caused by antiplatelet therapy through a randomized controlled design, in order to evaluate the risk of gastrointestinal injury and bleeding in CAD patients receiving different long-term antiplatelet therapy regimens after the implantation of contemporary DES, and provide clinical evidence for guidance of antiplatelet strategy after PCI.

## 1.1 Study Hypothesis

The principal hypothesis of this study is that following 6 months of DAPT, antiplatelet monotherapy with aspirin or clopidogrel between 6 and 12 months after DES implantation is superior to 12 months of DAPT for preventing gastrointestinal injury detected by AMCE.

## 1.2 Rationale of Study

1. Gastrointestinal mucosal injury (represented by erosion, ulcer, or bleeding) is a common complication of long-term antiplatelet therapy after PCI.
2. Trials in patients treated with contemporary DES have demonstrated that shortened DAPT regimens reduce the risk of major bleeding with similar ischemic risk. However, whether there is no definite evidence by current studies exploring the difference of gastrointestinal mucosal injuries among different antiplatelet strategies, mainly because gastroscopy, the most common detection method for gastrointestinal mucosal injury, have considerable limitations including invasive characteristic, requirement for discontinuation of APT and inability of detection of small intestine, so that can hardly be widely used for patients with PCI.
3. ANKON® magnetically controlled capsule endoscopy (AMCE) is a novel, noninvasive, actively and precisely controlled system which could visualize gastrointestinal injuries in the gamut of esophagus, stomach and small intestine (except colon). Patient acceptance of AMCE is higher than standard endoscopy as the procedure involves only swallowing a small capsule endoscope with non-invasive, painless, convenient and repeatable image observation. Discontinuation of antiplatelet drugs during AMCE is not necessary, which is substantially avoid the potential ischemic risk induced by discontinuation.

Therefore, our study first proposes that, 6-month DAPT plus 6-month antiplatelet monotherapy could significantly reduce the risk of gastrointestinal mucosal injury compared with 12-month DAPT after implantation of newer-generation DES, and first use AMCE as the method for detection of gastrointestinal mucosal injury among CAD patients with PCI, and establish a score system based on results of AMCE, to evaluate the risk of gastrointestinal injury and bleeding.

### **1.3 Benefit/risk and ethical assessment**

The potential benefits that subjects might realize by participating in this randomized trial is a reduction in gastrointestinal mucosal injury for those who are randomly allocated to the experimental arm. Other benefits applicable to all subjects include the free antiplatelet medications after randomization, free inspections including AMCE examination for three times during the whole study period, fecal occult blood (FOB) and blood routine (BT) tests one time per two months, and close monitoring and surveillance for clinical events that will be performed by study personnel during the course of the trial.

The potential risks include an increased rate of thrombotic events for those who are randomized to the antiplatelet monotherapy arm and increased risk for bleeding in subjects randomized to the DAPT arm. However, based on current guidelines, increases of these potential risks are uncertain.

## **2. STUDY OBJECTIVES**

### **2.1 Primary Objective**

The primary objective of this study is to determine the risks of 12 months of DAPT vs 6 months of DAPT followed by 6 months of aspirin monotherapy or clopidogrel monotherapy on gastrointestinal mucosal injury after DES implantation.

### **2.2 Secondary Objective**

The secondary objective is to evaluate the feasibility and safety of AMCE as a method for detecting gastrointestinal mucosal injury and bleeding in patients receiving APT.

### **2.3 Exploratory Objective**

The exploratory objective is to establish a gastrointestinal mucosal injury scoring system that may identify patients at future risk for clinical gastrointestinal bleeding during long-term APT.

### 3. STUDY DESIGN AND FLOW CHART

[figure not shown]

**Study flowchart.** PCI: percutaneous coronary intervention; DES, drug-eluting stent; GI: gastrointestinal; AMCE: ANKON magnetically controlled capsule endoscopy.

### 4. SUBJECT SELECTION CRITERIA

A subject is considered enrolled if all requisite inclusion and none of the exclusion criteria are met and upon provision of informed consent.

#### 4.1 Inclusion criteria

1. Adult patients with age 18–80 years;
2. Presentation with stable angina, or non-ST-segment elevation acute coronary syndrome with GRACE score <140 at admission;
3. PCI with implantation of contemporary drug-eluting stent(s) during the present admission (contemporary DESs refer to drug-eluting stents with biodegradable polymer and (or) high biocompatibility and (or) thin cobalt-chromium or platinum-chromium struts. The current major DESs available in China market include: EXCEL (JW Medical System, Weihai, China), Tivoli (Essen Technology, Beijing, China), Endeavor Resolute (Medtronic Inc, Minnesota, USA),

FireHawk (MicroPort Medical (Group) Co, Ltd, Shanghai, China), Xience V (Abbott, Abbott Park, Illinois, USA), Xience Prime (Abbott Laboratories, Abbott Park, Illinois, USA), Promus Element and Synergy (Boston Scientific, Massachusetts, USA), Nano (Lepu Medical Technology CO., LTD, Beijing, China), etc.);

4. Complete revascularization (successful PCI treatment of all epicardial coronary lesions with diameter stenosis  $\geq 70\%$  or intermediate lesions with FFR  $< 0.80$ );
5. Planned DAPT with aspirin and clopidogrel for at least 6 months;
6. Agreement to comply with all study procedures;
7. Written informed consent provided.

## 4.2 Exclusion criteria

1. Presentation with STEMI, or NSTEMI-ACS with GRACE score  $\geq 140$ ;
2. Left main disease (diameter stenosis  $> 30\%$ );
3. Any prior coronary stent implantation during the last year prior to the index procedure;
4. Implantation of first-generation drug-eluting stents or bioabsorbable scaffolds during the index procedure;
5. Implantation of  $> 4$  stents during the index procedure;
6. Any prior stent thrombosis;
7. Any active gastrointestinal bleeding or ulcers, or prior gastrointestinal bleeding or ulcers within the last 24 months;
8. Prior gastrointestinal tract or abdominal surgery other than simple procedures which would not change the gastrointestinal tract anatomy, such as polyp removal, cholecystectomy or appendectomy;
9. Contraindications to the AMCE test, including suspected or known gastrointestinal obstruction, stenosis, fistula, diverticula, etc.; presence of gastrointestinal obstruction symptoms such as pain or dysphagia; inoperative conditions or refusal to undergo abdominal surgery if required (because once the capsule could not pass the tract, a surgery may be needed);
10. Severe hemorrhoids (phase 3–4 according to guidelines of American Society of Colon and Rectal Surgery);
11. LVEF  $< 0.40$  on admission by echocardiography;

12. Renal dysfunction (eGFR <30 ml/min/1.73m^2);
13. Active hepatitis or ALT >3 times upper limits of normal at admission;
14. Severe hypertension (>180/110 mmHg), or hypertension without control;
15. Hemoglobin <100 g/L;
16. Platelet count <100 × 10^9/L;
17. Unable to restrict use of PPI, gastric mucosa protectant or any other antacid agent by rule (details in “restrictions during the study”)
18. Required use of oral anticoagulation (warfarin or other factor II or factor X inhibitors);
19. Inability to take 12-month DAPT for any reason;
20. Mandatory use of >6-month DAPT (indicating those who are not suitable to receive aspirin or clopidogrel monotherapy);
21. Any comorbidity with estimated survival time <12 months (e.g., progressive cancer, chronic obstructive lung disease, etc.);
22. Any contraindication to MRI examination, including implantation of an MRI-incompatible pacemaker, defibrillator, or other ferromagnetic material, etc.;
23. Pregnant or plan to be pregnant;
24. Any condition that may interfere with any study procedures, such as dementia, immobility, alcohol use, etc.;
25. Planned surgery within 1 year;
26. Taking iron supplement;
27. Participating in any other clinical trial of an investigational drug or device that has not met its primary endpoint.

## **5. STUDY CONDUCT**

### **5.1 Restrictions during the study**

Enrolled subjects should remain on routine aspirin plus clopidogrel for the first 6 months after index PCI, and blinded study drug for the 6 months after randomization (the second 6 months after PCI).

Unless clinically indicated, PPIs or any other type of gastric mucosal protectants should not be taken by study participants during the course of the trial. Once these drugs are taken, it should not be administered continuously for more than 4 days or a total of more than 12 days before randomization (the first 6 months PCI); it should not be taken for more than 4 days continuously or in total of more than 10 days within 6 months after randomization. Otherwise, any condition that is not in accordance with restrictions above will be considered as a violation of the study protocol, and subjects with this condition will be suspended early from this study.

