| Evaluation of Randomization Eligibility | 
Eligibility for randomization will be evaluated in all enrolled patients at 6 months after PCI. At this time patients with any of the following exclusion criteria will be suspended for randomization.
 
 
1. Withdrawal of informed consent;
 
2. Lost to follow-up at 6 months;
 
3. Any event in the prior 6 months which in the opinion of the investigator results in the patient not being suitable for randomization of antiplatelet agent regimen either because of a) necessity to continue dual antiplatelet therapy (e.g., major adverse cardiovascular or cerebrovascular event within the prior 6 months or need for repeat stenting), or b) inability to continue dual antiplatelet therapy (e.g., bleeding, neoplasm, need for urgent surgery, etc. within the prior 6 months);
 
4. Not presently taking both aspirin and clopidogrel, or any prior temporary discontinuation of aspirin or clopidogrel for <math>\geq 5</math> days;
 
5. Use of proton pump inhibitors or gastric mucosal protectants for more than 12 days, or for more than 4 continuous days in the 6 months prior to randomization;
 
6. Unwillingness or inability to undergo the 6-month AMCE examination or the remainder of the study procedures, including the 12-month AMCE exam.
 
 |

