## **5.3 Subject randomization and initiation of investigational product**

A second AMCE examination will be performed to evaluate eligibility for randomization in all enrolled patients at 6 months after PCI. Subjects with any one of items below should not be randomized:

1. Withdrawal of informed consent;
2. Lost to follow-up at 6 months;
3. Any event in the prior 6 months which in the opinion of the investigator results in the patient not being suitable for randomization of antiplatelet agent regimen either because of a) necessity to continue dual antiplatelet therapy (e.g., major adverse cardiovascular or cerebrovascular event within the prior 6 months or need for repeat stenting), or b) inability to continue dual antiplatelet therapy (e.g., bleeding, neoplasm, need for urgent surgery, etc. within the prior 6 months);
4. Not presently taking both aspirin and clopidogrel, or any prior temporary discontinuation of aspirin or clopidogrel for  $\geq 5$  days;
5. Proton pump inhibitors or any other kind of gastric mucosal protectant agents may not be used after study enrollment unless a clear clinical indication has developed (e.g., new gastrointestinal bleeding or ulcer disease). After

randomization, gastric mucosa protectants may not be taken for more than 4 days continuously or in total for  $\geq 10$  days without a clear clinical indication.

6. Unwillingness or inability to undergo the 6-month AMCE examination or the remainder of the study procedures, including the 12-month AMCE exam.

Patients successfully completing the 6-month follow-up AMCE exam and with no ulceration or bleeding (approximately 480 patients) are then randomly assigned in a 1:1:1 ratio to receive three antiplatelet strategies below: Group A, the standard DAPT (160 patients, aspirin plus clopidogrel); Group B, aspirin monotherapy (160 patients, aspirin plus clopidogrel-placebo); and Group C, clopidogrel monotherapy (160 patients, clopidogrel plus aspirin-placebo) for an additional 6 months in a double blinded manner. A third AMCE examination will be done at 12 months after enrollment.

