### **5.5.2 Methods for breaking the blinding in the study**

In the event of a medical emergency, in which knowledge of the investigational drug is critical to the subject's medical management, the blind for that subject may be broken by the treating physician. Before breaking the blinding, the consent of the research leader of the participating research site should be obtained and the relevant researchers and monitors should be informed. At the same time, the events leading to break the blinding and the blind code information should be recorded in detail. After breaking the blinding, the subject will not receive any study drug, and the treated physician can take corresponding bail-out measures according to local standard of care. The study drugs cannot be resumed even if the condition of subject is stable, while researchers still need to conduct clinical follow-up for 12 months for the subject with broken blinding, and AMCE examination is still required. Researchers should withdraw the study drugs from the patients whose blinding was broken.

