### **5.9.2 Permanent discontinuation from study medication due to reasons below:**

- Patient decision. The patient is at any time free to discontinue treatment, without prejudice to further treatment.
- Investigator's decision:
  - 1) Incorrectly enrolled patient in whom the inclusion/exclusion criteria violation would put the patient at undue risk.
  - 2) Investigators judge that due to adverse events related to any kind of study drug, continuous administration of this study drug would put the patient at undue risk.

Details on the date, duration and cause of each permanent discontinuation of study drugs should be fully recorded into the appropriate section of the EDC. When any of the study drugs are permanently discontinued, further antiplatelet therapy should be given to the subject according to attending physician's discretion. Any remaining study drugs should be returned to the local research site at the next scheduled follow-up visit. Although these subjects are no longer receiving any study drug, they should also be followed up until 12 months. Patients who permanently discontinue study drugs after randomization are still required to undergo AMCE examination, and investigators are required to withdraw study drugs from patients after discontinuation. Patients who permanently discontinue study drugs before randomization only needed to be followed up by telephone at 12 months.

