## **5.10 Withdrawal from study**

Each enrolled subject shall remain in the trial until completion of the required follow-up period. However, a subject's participation in any clinical trial is voluntary and the subject has the right to withdraw at any time without penalty or loss of benefit. Conceivable reasons for discontinuation may include, but not be limited to, the following:

- Subject voluntary withdrawal
- Subject withdrawal by physician as clinically indicated
- Subject lost-to follow-up

The reason for subject discontinuation must be documented on the CRF and source documents. The principal investigators must also report all subject discontinuations to their Ethical Committee as defined by their sites' procedure. All data from

evaluations and treatments performed prior to the withdrawal should be documented on the CRFs. Source documents that pre-date the withdrawal should be submitted as required by the protocol. No data that post-dates the withdrawal will be collected.

Once a subject has withdrawn from the trial, no further follow-up contact will be performed. However, vital status may be obtained from public records. Medical therapy after stopping the study will be as prescribed by the subject's physician.

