## **18.4 Judgment criteria and treatment rules of severe gastrointestinal mucosal lesions requiring PPI**

**Principles of PPI:** PPI and/or gastric mucosal protective agent should only be added to diagnosed ulcer lesions. No special treatment will be given if only an erosion exists.

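### Protocol 5.1 suspends randomised patients who exceed the PPI day limit without keeping their 12-month AMCE, which can drop lesion-free patients from the primary analysis

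*Supplement*

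**What the plan says.** **The rule.** Protocol v1.4 section 5.1 opens with "Unless clinically indicated, PPIs or any other type of gastric mucosal protectants should not be taken by study participants". It then sets day limits: before randomisation, 4 continuous or 12 total days; after it, 4 continuous or 10 total days. Anything beyond these limits "will be considered as a violation of the study protocol, and subjects with this condition will be suspended early from this study". The clinical-indication qualifier is not repeated in the sentences on limits and suspension, and the 12-month AMCE is not mentioned.

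**Neighbouring rules that keep the scan.** Section 5.5.2 requires 12 months of clinical follow-up "for the subject with broken blinding, and AMCE examination is still required". Section 5.9.2 says: "Patients who permanently discontinue study drugs after randomization are still required to undergo AMCE examination". Its listed reasons (patient decision, incorrect enrolment, drug-related adverse event) do not include PPI overuse.

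**Withdrawal.** Section 5.10 states: "No data that post-dates the withdrawal will be collected".

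**A second version of the limit.** Section 5.3 item 5, in the list of reasons not to randomise, bars use after randomisation for more than 4 continuous days or a total of 10 or more "days without a clear clinical indication". Section 5.1 says more than 10.

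**Analysis.** SAP 6.1 includes all randomised patients in the FAS whatever their adherence, but restricts the primary endpoint to an mITT set with valid results. SAP 4.1 lists three valid situations: a completed 12-month AMCE with any finding; no 12-month AMCE but a new lesion at month 6; or a new lesion at a bleeding-driven examination. The per-protocol exclusions in SAP 6.2 do not mention PPI use.

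**The concern.** A patient who overuses a PPI after randomisation has done something that may reflect gastrointestinal symptoms, and so may be related both to treatment and to the endpoint. If such patients leave without the final scan, SAP 4.1 treats them unequally: those with an earlier lesion count as events, and those without one disappear from both numerator and denominator. Membership of the primary analysis set would then depend on a post-randomisation event and on the outcome itself.

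The rule also sits in an odd place. PPI overuse has no consequence for the per-protocol set, where a breach of this kind would normally be handled, yet it can remove a patient from the primary set. In addition, sites reading 5.1 and 5.3 differently on clinical indication could treat the same patient differently.

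**Working it through.** **1. The plan's own figure.** Inputs from protocol 12.3 and SAP 5: 47% (DAPT) v 30% (pooled monotherapy), 128 v 256 evaluable, two-sided 0.05.

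Power = Φ{[Δ − 1.96·√(p̄(1−p̄)(1/n₁+1/n₂))] / √(p₁(1−p₁)/n₁ + p₂(1−p₂)/n₂)}.

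Here p̄ = (128×0.47 + 256×0.30)/384 = 0.357. The null standard error is 0.0519 and the alternative standard error 0.0526, so power = Φ[(0.17 − 0.1016)/0.0526] = Φ(1.30) = 0.903. Solving for 90% gives 127 + 254 = 381, against 384 stated, and 384/0.80 = 480. The plan's numbers reproduce.

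**2. Who leaves, reading 5.1 as exit from the study.**

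| Randomised patient over the limit | Valid under SAP 4.1? | In the mITT? |
|---|---|---|
| New erosion at month 6 (ulcer or bleeding bars randomisation) | yes | yes, as an event |
| New lesion at a bleeding-driven examination | yes | yes, as an event |
| Neither, 12-month scan not done | no | leaves |

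**3. Illustrative size.** The documents give neither a PPI-overuse rate nor a month-6 erosion rate among randomised patients, so everything in this step is assumed. Let P be the 12-month incidence; e the share already lesion-positive at month 6 (10% to 25%, equal in both arms because it precedes randomisation); and s₁, s₀ the breach shares of patients who are and are not injured by month 12, equal in both arms. Lesions at bleeding-driven examinations are ignored; they would keep more patients in.

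Observed rate = [e + (P−e)(1−s₁)] / [e + (P−e)(1−s₁) + (1−P)(1−s₀)].

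Worked case, s₁ = 10%, s₀ = 2%, e = 10%:
- DAPT: 0.10 + 0.37×0.90 = 0.433; 0.53×0.98 = 0.519; rate 0.433/0.952 = 45.5%.
- Monotherapy: 0.10 + 0.20×0.90 = 0.280; 0.70×0.98 = 0.686; rate 0.280/0.966 = 29.0%.
- Difference 16.5 points.
- Suspended: 160×0.0576 + 320×0.0440 = 23. Leaving the mITT: 160×0.0476 + 320×0.0340 = 19.

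Ranges below are over e. Power is given first with the losses inside the 20% allowance (128 v 256 kept), then with them on top of it.

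| Breach, injured / uninjured | Suspended of 480 | Leave mITT | Difference (points) | Power inside | Power on top |
|---|---|---|---|---|---|
| design | – | – | 17.0 | 0.90 | – |
| 5% / 5% | 24 | 18–22 | 16.8–16.9 | 0.89–0.90 | 0.88–0.89 |
| 10% / 2% | 23 | 11–19 | 16.2–16.5 | 0.88–0.89 | 0.87–0.88 |
| 30% / 5% | 67 | 31–52 | 14.5–15.1 | 0.80–0.85 | 0.77–0.80 |
| 5% / 10% | 39 | 33–37 | 17.0–17.1 | 0.90 | 0.88 |

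**4. Direction.** Let a share s of an arm leave with lesion risk r, so that the observed rate is (P − s·r)/(1 − s). Suppose 10% of DAPT and 5% of monotherapy patients leave.
- Leavers at high risk (70% and 50%): (0.47−0.07)/0.90 = 44.4% v (0.30−0.025)/0.95 = 28.9%, or 15.5 points.
- Leavers at low risk (30% and 20%): (0.47−0.03)/0.90 = 48.9% v (0.30−0.01)/0.95 = 30.5%, or 18.4 points.
- Removing 5% of each arm, all injured, also raises the difference: 0.42/0.95 = 44.2% v 0.25/0.95 = 26.3%, or 17.9 points.

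The sign therefore depends on facts the documents do not give.

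**The case against.** **The loss of the scan is inferred.** Section 5.1 mentions neither withdrawal nor cancelling the AMCE, and 5.10 does not name a PPI breach. The synopsis says that patients who fail month-6 eligibility "will be suspended for randomization", and 5.3 still follows those patients to 12 months. Where the protocol plainly omits the scan, after a post-randomisation bleed, section 18.2 says so. This stands as a limit on certainty. But 5.1 says suspended from the study, not from randomisation or drug, and no text tells a site to scan these patients.

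**The SAP includes patients whatever their adherence.** True of the FAS in 6.1, but the same section then requires a valid result for the primary endpoint.

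**The route is narrow.** This largely stands. Section 18.4 says of erosions: "No special treatment will be given if only an erosion exists". Patients unable to restrict PPIs are excluded at entry. Indicated courses may be exempt under 5.3. The endpoint definition also counts clinically driven endoscopy, so a symptom-led examination that finds a lesion may count.

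**Allowance and sensitivity analyses.** The 20% allowance protects numbers, not against selective loss. The best-case, worst-case and tipping-point analyses in SAP 8 would show how much the missing results matter, but recover no scan.

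**Stronger readings that a reader might infer.** One is that *H. pylori* eradication, a 2-week course with a PPI that the SAP 7 footnote allows at physician discretion, would routinely trigger suspension. The documents do not support this. *H. pylori* is tested only at Visit 1, so a course prompted by that test would usually fall before randomisation. Section 18.4 describes the course under ulcer treatment, and 5.3 names ulcer disease as a clear indication. Another is that the rule biases the trial in a known direction or seriously weakens it; the scenarios above do not show that.

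**Conclusion.** The point holds in a limited form. Section 5.1 sets a consequence for PPI overuse that, on its natural reading, costs the 12-month AMCE. Under SAP 4.1 and 6.1, suspended patients then remain in the primary analysis only if they already have a lesion. This is an avoidable, outcome-dependent exclusion after randomisation, created by a stated rule.

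Its size is probably small. In the milder scenarios (5% in all, or 10% v 2%) the difference moves by less than one point and power stays at 0.87 or above. A serious effect needs something like 30% breach among injured patients, for which the documents give no support. Direction is unknown.

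The conclusion rests on reading *suspended* as leaving the study, which the protocol does not define. The sizes rest on assumed breach and month-6 erosion rates. The change is worth making because it is cheap and the harm preventable, not because the primary result is shown to be at risk.

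**What to change.** In protocol 5.1, replace the suspension of randomised patients with: *PPI or mucosal protectant use beyond the limit after randomisation is recorded as a protocol deviation; the patient stays in the study, has the 12-month AMCE and is kept in the primary analysis.*

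Optionally, add the breach to the per-protocol exclusions in SAP 6.2 and report breaches by arm.

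As an editorial step, align 5.3 item 5 with 5.1. Use the synopsis and SAP 3.3 wording for use before randomisation. Keep a single post-randomisation limit in 5.1, with one statement on whether clinically indicated use counts. No separate rule for *H. pylori* eradication days is needed; it could contradict that statement.

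Cost: wording in two protocol sections and, optionally, one SAP section, with the usual ethics approval of an amendment. The 12-month AMCE and the concomitant-medication record are already in Table 2, so no visit or data item is added.
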